### Public involvement

All patients will participate in the study voluntarily and sign an informed consent form. This study will be based on patient and public participation. We will complete the questionnaire by asking patients questions and promoting medical knowledge by establishing good relationships with patients.

### Study follow-up assessments

When a patient has FT_4_ levels below the lower limit of the normal reference range during follow-up, follow-up is terminated and thyroid hormone replacement therapy will be initiated. For patients aged 60 to 70 years, start treatment when TSH≥10mIU/L. For patients aged 71 to 80 years, treatment begins when TSH≥10 mIU/L and is accompanied by symptoms of hypothyroidism. Normal value reference ranges will be established based on the TSH levels of 120 normal elderly individuals over 60. Elderly SCH patients screened according to the TSH reference interval in the normal population and the elderly population will be followed up every 6 months, including the subclinical hypothyroidism questionnaire, the Montreal Cognitive Assessment-Basic (MoCA-B), Hamilton Depression Scale (HAMD), Hypothyroidism Symptom Questionnaire (SRQ), frail scale(FRAIL), fatigue scale, EQ-5D, thyroid function, blood lipid analysis, carotid color ultrasound, and thyroid ultrasound. The estimated sample size is 438. Patients diagnosed with different TSH reference intervals will be compared for cognitive function, depression scores, hypothyroidism, fatigue severity, carotid atherosclerosis, lipid profile, and cardiocerebrovascular complications. Besides, TSH reference intervals will be applied to calculate medical costs and evaluate the economic benefits of multiple follow-ups of patients with SCH. The research design can be seen in **Figure 1**.

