6 (15)	2021	Endocrine Metabolic Diseases Group of the Chinese Geriatrics Society, Thyroid Group of the Chinese Society of Endocrinology, Chinese Medical Association	60-70 years old: treat if TPOAb(+) or there are hypothyroidism symptoms or cardiovascular risk factors; otherwise, observe	60-70 years old: treat
			71-80 years old: observe	71-80 years old: treat if there are hypothyroidism symptoms or cardiovascular risk factors; otherwise, observe
			Age>80 years: obersve	Age>80 years: obersve

In the process of SCH, we need to consider the adverse outcomes of cardiovascular and cognitive functions. The thyroid hormone is closely related to the cardiovascular system and plays a key role in the regulation of cardiac muscle cell inotropic and chronotropic effects (21, 22). SCH is generally considered a risk factor for cardiovascular disease and cardiovascular-related death events. At present, some studies have shown that the prediction of cardiovascular disease and mortality in elderly patients with SCH should be based on age and TSH level (23–26). The prognosis of the elderly is good, and TSH>10mU/L is often associated with the occurrence of cardiovascular diseases, which need further confirmation. For cognitive function, the thyroid hormone plays a key role in brain development and maturation, so abnormal thyroid function and hormone secretion may affect the neuropsychiatric system (27). Although thyroid function examination is usually performed in patients with cognitive impairment or depression, the relationship between SCH and neurological and psychological functions is still unclear. However, previous research suggested that SCH in the elderly has nothing to do with cognitive decline or dementia events, so it may not be necessary to conduct SCH screening in the elderly with cognitive decline (28–30). It is noteworthy that some studies have found that elderly patients with SCH may be prone to depression, but the results are inconsistent (31–33). Therefore, our research will focus on the cardiovascular disease and depression of patients.

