### Research objectives and main results

The goal of this study is to prospectively follow up on elderly patients with SCH who are diagnosed using age-specific TSH reference intervals and non-age-specific TSH reference intervals, which aims to establish TSH reference intervals for different age groups to improve the diagnosis and management of SCH in the elderly. The main outcomes being assessed include thyroid function, hypothyroidism-related symptoms, cardiovascular events, cognition, depression, and fatigue, as well as economic and social benefits analysis. The above information will help make informed decisions about the best course of treatment for elderly patients with SCH.

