### Data analysis

We will calculate age-specific TSH reference intervals based on the obtained data, analyze the natural outcomes, the occurrence of cardiovascular events, cognitive status, depression, and fatigue of elderly patients with SCH diagnosed under different reference intervals, and conduct economic analysis.

Continuous data will be expressed as mean ± standard deviation or median with a range of quartiles. Classification data will be expressed in numbers with percentages. Cox proportional risk model will be used to evaluate survival results. The variables measured several times during the follow-up period will be compared with the paired t-test according to the clinical management used. The significance level will be set to 0.05, and R software, prodlim, and Cairo software will be used to analyze the data.

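### Cardiovascular events are a main outcome, but the visit schedule names no source for them or for vital status, and the exclusion and stopping rules let patients who die or stop attending drop out uncounted

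*Protocol article*

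**What the plan says.** Research objectives and main results: "The main outcomes being assessed include thyroid function, hypothyroidism-related symptoms, cardiovascular events, cognition, depression, and fatigue".

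Introduction: cardiovascular disease is one of two stated points of focus ("our research will focus on the cardiovascular disease and depression of patients"). Cardiovascular death appears there as background ("SCH is generally considered a risk factor for cardiovascular disease and cardiovascular-related death events") and is not listed as a study outcome.

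Study follow-up assessments: patients "will be followed up every 6 months, including the subclinical hypothyroidism questionnaire, the Montreal Cognitive Assessment-Basic (MoCA-B"), then further scales, closing with "EQ-5D, thyroid function, blood lipid analysis, carotid color ultrasound, and thyroid ultrasound". The same section says that the diagnostic groups will be compared for, among other things, "carotid atherosclerosis, lipid profile, and cardiocerebrovascular complications". It also ends follow-up when FT4 drops below the lower reference limit.

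Data analysis: the study will "analyze the natural outcomes, the occurrence of cardiovascular events, cognitive status, depression, and fatigue of elderly patients with SCH", and "Cox proportional risk model will be used to evaluate survival results". That last sentence does not name the event.

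Inclusion criteria and exclusion criteria: exclusion items (2) and (3) are leaving the study midway for whatever reason, and being unable to complete all the examinations.

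**The concern.** Every other clinical main outcome has a named instrument in the six-monthly schedule. Cardiovascular events do not. The most serious events (death, disabling stroke, long admission) are also the ones most likely to stop a patient attending or completing a battery of scales and ultrasounds, and the exclusion list treats both as grounds for exclusion.

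The study wants to separate older patients whose raised TSH matters from those in whom it does not. That depends on their prognosis. If fatal and disabling events leave the data along with the patient, prognosis looks better than it is. If the loss differs between the diagnostic groups, the comparison between them is distorted as well.

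**Working it through.** This is a question of data collection, so the check is mainly to set the sections side by side.

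**Step 1. Match each main outcome to the six-monthly schedule.**

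| Main outcome | Item named in the schedule |
|---|---|
| Thyroid function | Thyroid function tests |
| Hypothyroid symptoms | SRQ |
| Cognition | MoCA-B |
| Depression | HAMD |
| Fatigue | Fatigue scale |
| Cardiovascular events | None; only lipids and carotid ultrasound |

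The lipid and carotid measures cannot be meant as the events, because the comparison list ("carotid atherosclerosis, lipid profile, and cardiocerebrovascular complications") counts clinical complications as a third, separate item. The Abstract's list of questionnaires and tests has no event item either, and the endpoint events that it defines rest on TSH and FT4 alone.

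**Step 2. Follow a patient with a serious event through the text.** A patient enrolled in early 2023 dies or has a disabling stroke between visits.
- No scheduled item is named that would record it.
- The patient has left midway (exclusion item 2) or cannot complete all examinations (item 3). Leaving midway can only happen after enrolment, so item 2 acts as a post-enrolment removal. Item 3 could be a baseline test of feasibility, but its wording does not limit it to that.
- The patient can therefore be dropped from numerator and denominator alike.

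**Step 3. Follow a patient whose FT4 falls.** Follow-up ends there, so a later cardiovascular event is outside the data. If FT4 falls more often in one diagnostic group, observation is shorter in that group.

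**Step 4. Size.** The documents give 438 patients and, from the recruitment and closing dates, 2 to 3 years of follow-up each. They give no cardiovascular event rate, mortality or case fatality, so there is no figure to reproduce. For scale only, on assumed rates:
- First events = 438 × (1 − exp(−rate × years)). At 1% a year for 2 years: 438 × (1 − exp(−0.02)) = 8.7. At 5% a year for 3 years: 438 × (1 − exp(−0.15)) = 61.0.
- If 20% to 40% of these were fatal: 0.2 × 8.7 = 1.7 up to 0.4 × 61.0 = 24.4.
- If patients with fatal events are removed, the observed risk is p(1 − f)/(1 − pf), where p is the true risk and f the fatal share. Take two groups with the same p, one with f = 0.2 and the other with f = 0.4. At p = 61.0/438 = 0.139 the observed risks are 0.115 and 0.089, a ratio of about 1.3. At p = 8.7/438 = 0.020 they are 0.0159 and 0.0120, again about 1.3.

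On these assumptions, removal alone could create an apparent difference of about 30% between groups with equal true risk. If f were the same in both groups, the ratio would be nearly preserved and only the absolute risks would be too low.

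**The case against.** The strongest reply is that this is a condensed article. The schedule is introduced as a list of inclusions, not as complete. The content of the subclinical hypothyroidism questionnaire is not shown, nor is the study-process figure, and an event form may sit in the full protocol. The article also commits to comparing complications and analysing events, which implies that someone will collect them. All of this stands. A reader might infer that events and deaths are not collected and are therefore missed; the documents do not support that.

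A reader might also infer that the study is heading for a no-harm conclusion based on survivors. No no-harm or non-inferiority conclusion is stated. The aims are age-specific intervals, natural outcomes, less overdiagnosis and economic benefit. Death is background, not a promised outcome.

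Nor can expected deaths be ranked against thyroid progressions. At an assumed 2% to 6% mortality a year and a mean of 2.5 years, deaths number 438 × (1 − exp(−0.05)) = 21 to 438 × (1 − exp(−0.15)) = 61. Scaling the cited cohorts (3.4% in 3 years, 26.8% in 6 years) to the same period at constant hazard gives 438 × (1 − 0.966^(2.5/3)) = 12 to 438 × (1 − 0.732^(2.5/6)) = 53 progressions. The ranges overlap.

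Finally, ending observation when replacement therapy begins is a reasonable choice for describing the untreated course.

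What the reply does not remove is the printed text on exclusions and stopping. That is not missing detail: applied as written, it can take patients with fatal or disabling events out of the study.

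**Conclusion.** The point holds as a mismatch between sections. The article names cardiovascular events as a main outcome and plans to compare them, states no source for clinical events or vital status, and has exclusion and stopping rules that can remove the patients in whom such events occur. The likely direction is toward too favourable a prognosis, with a possible distortion of the group comparison.

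The size cannot be computed from the documents. The counts and the 1.3 ratio above rest wholly on assumed rates and on unequal fatal shares, and they show only that the effect need not be negligible. The conclusion assumes that exclusion items (2) and (3) are applied to enrolled patients, and that no event form exists outside the article. If one exists, what remains is to cite it and to reword the exclusions. This is a cheap improvement, not a fatal flaw.

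**What to change.** 1. In Study follow-up assessments, add a short dated form to the six-monthly schedule for cardiovascular and cerebrovascular events, cardiovascular admission, and death with cause. Existing staff complete it at the visit, and by telephone for patients who do not attend. If such a form already exists, cite it.
2. Record vital status for every enrolled patient at December 2025, including those who leave and those who reach the FT4 endpoint. This concerns data collection only and changes no treatment rule.
3. In the exclusion criteria, state that midway exit or incomplete examinations do not remove an enrolled patient from the event analysis.
4. Report death alongside the cardiovascular events. It need not become a new main outcome.

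Cost: one extra form, some telephone calls and slightly more data entry. Reported event rates may look less favourable. Events not recorded during follow-up may be hard to recover later, so the change is worth making before data collection closes.

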**Methods:**

This is a multicenter prospective study that focuses on Chinese elderly patients with SCH who have TSH levels below 10 mU/L. After obtaining the informed consent of the patients, their initial diagnosis information will be registered, and they will be asked to fill out questionnaires such as the Montreal Cognitive Assessment-Basic (MoCA-B), Hamilton Depression Scale (HAMD), Hypothyroidism Symptom Questionnaire (SRQ), frail scale(FRAIL), fatigue scale, and EQ-5D. In addition, thyroid function tests, blood lipid analysis, carotid artery ultrasound, and thyroid ultrasound examinations will be conducted. Patients will also be grouped according to FT_4_ levels, the changes in FT_4_ and its relationship with TSH can also be described. For patients over 80 years old, a decrease in FT_4_ will be used as an endpoint event, while for patients between 60-80 years old, TSH levels greater than or equal to 10mIU/L or a decline in FT_4_ will be used as the endpoint event. The TSH reference intervals of the general and elderly populations will be used to calculate medical costs associated with multiple follow-ups of patients, and a social-economic analysis will also be conducted.

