## Introduction

Subclinical hypothyroidism (SCH) is characterized by elevated serum thyroid-stimulating hormone (TSH) and normal thyroid hormone levels (1). As TSH is considered a good indicator of thyroid function, the diagnosis of SCH is primarily based on TSH levels. However, this can lead to overdiagnosis and overtreatment in elderly patients with SCH, as their TSH levels may naturally increase with age without indicating an underlying thyroid dysfunction (2).

Many studies have found that the incidence rate of SCH increases significantly with age (3, 4), which suggests that we need to consider the impact of aging on the hypothalamic-pituitary-thyroid (HPT) axis. For example, aging may weaken the circadian rhythm of TSH and reduce its responsiveness (5). According to the cross-sectional National Health and Nutrition Examination Survey (NHANES) III, the average TSH of adults aged 80 is 69% higher than that of adults aged 20 (6, 7). Data from Scottish, and Australia also confirm that TSH level increases with age (8–10). Our previous epidemiological survey in ten cities indicated that the prevalence of SCH in people over 65 years old was 19.87% according to the current TSH reference interval, but when the age-specific TSH reference range was used, the prevalence decreased to 3.3% (3). Although the mechanism is unclear, the increase in TSH in the elderly may be a normal phenomenon associated with aging. When the current diagnostic criteria are used, many elderly patients with no clinical significance will be diagnosed.

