### Inclusion criteria and exclusion criteria

Inclusion criteria:

Elderly patients with SCH will be included according to the elderly and the general population-specific reference ranges, respectively.

(1) Inpatients and/or outpatients aged≥60 years.(2) The levels of free triiodothyronine(FT_3_) and FT_4_ are within the normal range.(3) TSH is greater than the upper limit of the normal reference range (old standard) and less than the upper limit of the normal reference range (new standard).

Exclusion criteria:

(1) Does not meet the inclusion criteria, does not sign the consent form, or participates involuntarily.(2) Exit halfway due to various reasons.(3) Unable to cooperate with the project team to complete all inspection contents.(4) Other factors leading to TSH increase. 1) increased TSH caused by measurement errors; 2) convalescence stage of the euthyroid sick syndrome; 3) central hypothyroidism; 4) renal insufficiency; 5) lack of glucocorticoids; 6) the recovery stage of thyroid function in subacute thyroiditis; 7) having taken amiodarone or lithium; 8) other interfering factors.

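### Clinical outcomes are compared only by TSH interval label, a contrast that could be imprecise and cannot show whether the age-specific limit is well placed; add an analysis on continuous entry TSH

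*Protocol article*

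**What the plan says.** - **Size.** The Methods section on study follow-up assessments gives one total: "The estimated sample size is 438". It gives no group sizes and no inputs.
- **Comparison.** The same section says that "Patients diagnosed with different TSH reference intervals will be compared for cognitive function, depression scores, hypothyroidism, fatigue severity", and continues with carotid, lipid and vascular outcomes. The contrast is by interval label.
- **Entry.** The eligibility section opens with "Elderly patients with SCH will be included according to the elderly and the general population-specific reference ranges, respectively". Its criterion (3) then requires that "TSH is greater than the upper limit of the normal reference range (old standard) and less than the upper limit of the normal reference range", the second limit being the new standard. The abstract describes the cohort as "Chinese elderly patients with SCH who have TSH levels below 10 mU/L".
- **Prevalence.** The Introduction reports from the group's own survey that "the prevalence of SCH in people over 65 years old was 19.87% according to the current TSH reference interval", and that "when the age-specific TSH reference range was used, the prevalence decreased to 3.3" per cent.
- **Use of TSH as a quantity.** The abstract plans to describe FT4 in relation to TSH, and the Limitations section plans an indicator combining T4 and TSH. The Data analysis section names a Cox model, without covariates, and paired t-tests. None of these relates cognition, depression, fatigue, carotid disease or lipids to TSH on a continuous scale.

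**The concern.** The study wants to know whether an age-specific limit picks out the older patients whose raised TSH matters. A comparison by label is a weak instrument for this, for two reasons.

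First, the group above the age-specific limit may be small. Precision would then rest on that group, whatever the total.

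Second, patients between the limits run from just above the old limit to just below the new one. A difference between the two group means does not say where along TSH the outcomes begin to worsen. A limit set too high can still produce a clear difference and appear to be confirmed. The patients wrongly reassured would be those just below it.

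**Working it through.** **1. The plan's own figure.** 438 cannot be reproduced, because the article gives no effect size, SD, event rate, power, allocation or dropout. Several routes reach it only with inputs that are not stated. One example: a 0.3 SD difference at 80% power needs 175 per group, 350 in all, and 350/0.8 = 438 for two equal groups. This cannot be attributed to the plan.

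**2. Split if enrolment mirrored the survey.** Inputs: 438 (follow-up section); 19.87% and 3.3% (Introduction).
- Share above the age-specific limit among those above the current limit: 3.3/19.87 = 0.166.
- 438 × 0.166 = 72.7, so about 73 above and 365 between the limits.

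**3. Precision of that split** (disjoint groups, mean outcome, equal SD, two-sided 5%).
- Balanced equivalent: 4 × 73 × 365/438 = 243. Efficiency against an equal split: 243/438 = 0.56.
- 95% CI half-width: 1.96 × √(1/73 + 1/365) = 0.251 SD. For 219 against 219 it is 1.96 × √(2/219) = 0.187 SD.
- Difference detectable with 80% power: 0.359 SD, against 0.268 SD when balanced.
- Power for an assumed 0.3 SD difference: 65%, against 88% when balanced.

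**4. Range over the share above the limit.**

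| Share above | Patients above | Balanced equivalent |
|---|---|---|
| 0 (criterion (3) read literally) | 0 | 0 |
| 5% | 22 | 83 |
| 10% | 44 | 158 |
| 16.6% (survey ratio) | 73 | 243 |
| 25% | 110 | 329 |
| 33% | 146 | 389 |
| 50% | 219 | 438 |

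**5. What the label contrast cannot distinguish.** Take the 16.6% share and assume, for illustration only, a harm of 0.5 SD that begins at the cohort's median TSH, well below the new limit.
- All patients above the new limit are affected. Of the 0.834 between the limits, 0.5 − 0.166 = 0.334 are affected.
- Difference between labelled groups: 0.5 × (1 − 0.334/0.834) = 0.30 SD.
- Share of affected patients who sit below the new limit: 0.334/0.5 = 67%.

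A harm of 0.30 SD that starts exactly at the new limit gives the same 0.30 SD contrast. The first case is a misplaced limit and the second a well-placed one. The planned comparison sees no difference between them.

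**The case against.** **The survey ratio need not be the enrolled mix.** This stands. The survey figures are for people over 65, while the study takes hospital patients aged 60 or more, under a limit still to be derived from 120 normal older people. Referral of patients with higher TSH could raise the share above the limit, and the cap at 10 would lower it. A reader might infer that only about 73 patients will be above the limit. The documents do not support that, and the table in the working gives the range.

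**Group sizes may be fixed elsewhere.** The eligibility lead-in can be read as separate enrolment of two groups, the study-process figure is not shown, and a condensed article may omit allocation. This also stands, and silence is weak evidence that no allocation exists.

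**The spline belongs in the analysis plan.** This stands in part. Model details can be left there. The article itself, however, fixes the clinical contrast by label, and that choice limits what the study can show. It would be too strong to say that the TSH gradient goes unused, since FT4 and T4 are to be examined with it. The gap concerns the clinical outcomes.

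**The arithmetic covers one case.** If the labelled groups are nested, 73 against 365 is not the contrast. For time-to-event outcomes precision depends on events, for which the article gives no assumption. Both are fair limits on the figures.

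**A reader might infer that places should be reserved for patients above the limit.** That does not follow. At survey prevalence, 146 such patients would need about 146/0.033 = 4,424 people tested, against 438/0.1987 = 2,204 for 438 consecutive patients, within a one-year recruitment window. It would also cut the between-limits group from 365 to 292, and that group carries the overdiagnosis question. If places were held until recruitment closed and testing reached only the lower number, 73 and 292 patients would result, with 63% power at 0.3 SD against 65% without any reservation.

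**Conclusion.** The point holds as a shortcoming in how the clinical comparison is framed. It does not show that 438 is too small. Three parts carry different weight.

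- **Firm.** The stated clinical comparison is by label only, and such a contrast cannot show whether the limit is rightly placed. This does not depend on the split. The 0.30 SD and 67% example rests on an assumed 0.5 SD harm and change-point, and illustrates the mechanism only.
- **Firm, and to be settled first.** Criterion (3), read literally, leaves no group above the new limit. That conflicts with the eligibility lead-in and with the planned comparison.
- **Conditional.** At the survey ratio the comparison has the precision of about 243 patients in equal groups and a half-width of about 0.25 SD, for disjoint groups and a mean outcome. The true share could lie on either side.

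**What to change.** 1. Reconcile inclusion criterion (3) with its lead-in sentence, with the abstract's TSH cap and with the comparison in the follow-up section, so that it is clear which patients can enter.
2. Keep 438 and the planned group comparison. State the group sizes expected within 438 and whether the groups are disjoint or nested.
3. For each clinical outcome, add an age-adjusted analysis on entry log TSH as a continuous variable, for example with a restricted cubic spline. Report estimates with 95% CIs at the old limit, midway and at the new limit. Judge the limit from those intervals, by whether they exclude differences large enough to matter. A curve that looks flat, or a non-significant test, should not count as support.

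Entry TSH is already collected, so this needs no further patients or measurements. It remains usable up to the new limit even if no group above that limit is enrolled. The cost is a little more analysis work, with wide intervals where TSH values are sparse at the upper end.

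### The two TSH-interval groups will probably differ in age, and the methods named in the Data analysis section do not deal with it

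*Protocol article*

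**What the plan says.** The Study follow-up assessments section commits to the contrast: "Patients diagnosed with different TSH reference intervals will be compared for cognitive function, depression scores", followed by hypothyroidism, fatigue, carotid disease, lipids and cardiocerebrovascular complications. The Discussion part of the Abstract and the Data analysis section describe the same contrast.

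Two methods are named in Data analysis. For time to event: "Cox proportional risk model will be used to evaluate survival results", with no covariates listed. Repeatedly measured variables "will be compared with the paired t-test according to the clinical management used". Neither that section nor any other mentions adjusting, stratifying or matching for age.

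The Introduction gives the link between age and grouping: "the average TSH of adults aged 80 is 69% higher than that of adults aged 20". The form of the elderly limit is left open. Research objectives and main results says the study "aims to establish TSH reference intervals for different age groups", which suggests age bands. Study follow-up assessments describes one reference sample of 120 normal people over 60 and mentions no bands.

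**The concern.** This is an observational contrast. Its grouping variable, TSH, rises with age on the article's own account, and the outcomes compared (cognition, carotid disease, cardiocerebrovascular events) can plausibly be expected to worsen with age. A difference between the groups may then reflect age rather than the diagnostic meaning of the interval.

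Age also enters the endpoint. According to the Abstract, patients over 80 reach the endpoint only through a fall in FT4, whereas those aged 60-80 can also reach it through TSH of 10 or more. A group with more people over 80 therefore has fewer routes to an event, whatever its prognosis.

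At stake is the study's main question: whether the elderly interval picks out the patients who matter. An age imbalance could make the new interval look better or worse, depending on how the limit is drawn.

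**Working it through.** **Inputs from the article (Introduction, unless stated).** TSH 69% higher at 80 than at 20; SCH prevalence over 65 of 19.87% by the general interval and 3.3% by the age-specific one; enrolment at TSH below 10 (Abstract); total of 438 (Study follow-up assessments). The 438 is given without inputs and cannot be reproduced. It is used only in step 5.

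**1. Slope.** If the rise is log-linear: ln(1.69)/60 = 0.5247/60 = 0.00875 log units per year, or about 0.087 per decade.

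**2. Group shares.** 3.3/19.87 = 16.6% of those above the general limit are also above the elderly limit; 83.4% lie between the two.

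**3. Age gap at that slope.** Assumptions: age is 60 plus a gamma variable, mean 70, SD 7; log TSH is normal with SD 0.45 to 0.58; the general limit cuts off the top 19.87%; the elderly limit cuts off the top 3.3%, either overall (single) or at each age (the limiting case of age bands). Simulation gives:

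| Elderly limit | Older group | Gap (years) | Spurious hazard ratio at 7-10% per year |
|---|---|---|---|
| Single | above the limit | 0.9-1.3 | 1.07^0.9 = 1.06 to 1.10^1.3 = 1.13 |
| Varying with age | between the limits | 1.3-1.7 | 1.07^1.3 = 1.09 to 1.10^1.7 = 1.18 |

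The hazard ratio is for the older group against the younger, with no true TSH effect. The 7-10% per year is an assumption about cardiovascular events. The sign reverses because the gap between a fixed general limit and a rising elderly limit widens with age.

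**4. Sensitivity.** A second set-up has a longer age tail (60 plus an exponential, mean 9, cut at 95), median TSH 2.3 at age 60, log-SD 0.5, general limit 4.5, enrolment below 10, and the elderly limit at the 97.5th centile, overall or within the 60s, 70s and 80+. It gives:

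- At 0.05 per decade: between-limits patients 1.58 years older (banded) or 0.62 younger (single).
- At 0.10 per decade: 3.26 years older (banded) or 1.50 younger (single).
- Interpolated to the documented slope: 1.58 + 0.75 × (3.26 − 1.58) = 2.8 years (banded) and 0.62 + 0.75 × (1.50 − 0.62) = 1.3 years (single). A direct run at that slope gives 2.8 and 1.2.

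The signs agree with step 3. The banded gap is sensitive to the age spread and to the enrolment ceiling: 2.8 years gives 1.07^2.8 = 1.21 to 1.10^2.8 = 1.31.

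**5. Continuous outcomes.** Take the second set-up at 0.10 per decade, all 438 patients split 82.2%/17.8% (360 and 78), and a correlation r of 0.2 to 0.4 between age and outcome (assumption). Banded, r = 0.2: bias = 0.2 × 3.26/9.59 = 0.068 SD; standard error = √(1/360 + 1/78) = 0.125; ratio 0.54; two-sided rejection rate 8.5% against a nominal 5%. Banded, r = 0.4: 0.136 SD and 19%. Single limit: 0.03 to 0.06 SD and 5.7% to 7.9%.

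**6. Methods against the question.** A paired t-test compares two measurements on the same patient. It has no group term and no covariate. The article splits it by clinical management, not by interval. It therefore cannot deliver the between-interval comparison of the scales, lipids or carotid measures. A Cox model can carry age, but the article does not say that it will.

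**The case against.** The strongest reply is that this is silence in a condensed article. A reader might infer that the comparisons are planned as unadjusted. The documents do not support that: no section says so, a Cox model can take covariates, and a covariate list is commonly left to a full protocol or SAP. This stands for the Cox model. It does not cover the repeated measures, where the article names a specific test that cannot do the job.

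A reader might also infer that group membership depends on age by construction. That holds only with age-banded limits. With a single over-60 limit, membership depends on TSH alone; the age gap is then indirect, opposite in sign and modest, with false-positive rates not far above nominal.

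Three further points have force:

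- The article does not say which outcome the Cox model serves. The only endpoint events it defines are thyroid ones, so the hazard ratios above apply to cardiovascular events only. For the thyroid endpoint, age matters through its age-dependent definition, an effect not quantified here.
- Inclusion criterion 3 admits only patients between the two limits. Read literally, there is no above-limit group to compare, and adjustment cannot repair that. The sentence opening the same list says patients enter by both ranges, so the criteria contradict each other.
- When two diagnostic rules are compared, crude results are of interest too. That the difference will be read as a TSH effect is a prediction, not something the article states. This argues for showing both analyses.

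**Conclusion.** The point holds in limited form. The central contrast is between non-randomised groups that will probably differ in age. The named methods either omit age (Cox, as stated) or can neither compare the groups nor adjust (paired t-test).

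The size rests on assumed age and TSH distributions and an assumed age effect on outcome. At the documented slope, the main set-up gives a gap of roughly 1 to 1.7 years and a spurious cardiovascular hazard ratio of about 1.05 to 1.2, in opposite directions under the two readings of the elderly limit. A longer age tail with the ceiling at 10 takes the banded figures to about 2.8 years and 1.2 to 1.3. A hazard ratio near 1.5 should not be inferred: it needs a gap of about 4.5 years (1.10^4.5 = 1.54), reached only with a slope two to three times steeper than documented and the highest assumed hazard.

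The unsuitability of the paired t-test rests on no assumption. The change is worth making because the bias is foreseeable, its sign is unknown until the limit is defined, and the remedy is cheap.

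**What to change.** In Data analysis:

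- For between-interval questions on repeated scales, lipids and carotid measures, replace the paired t-test with a regression or mixed model comparing the groups at follow-up, adjusted for age (continuous), centre and the patient's own baseline value.
- Include age in the Cox models, as a covariate or by using attained age as the time scale, and stratify by centre. The attained-age scale needs no extra parameter.
- Report the age-adjusted contrast as the main result, with the unadjusted one beside it.

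Also state whether the elderly limit is single or age-banded, since this sets the direction of the imbalance. Reconcile inclusion criterion 3 with its opening sentence, because the contrast needs patients on both sides of the elderly limit.

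The analysis changes cost only wording: age is known from eligibility, and baseline values and centre come with the planned visits. Sex could be added if it is recorded, but the article does not name it as collected. The price is that the effect becomes conditional on age.
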